## 9.1 Loss to follow up definition

Failure to collect primary outcome data at 12 weeks due to participant non-attendance at follow up.

## 9.2 Participant withdrawal and changes in levels of participation

Informed consent is defined as the process of learning the key facts about a clinical trial before deciding whether or not to participate. It is a continuous and dynamic process and participants should be asked about their ongoing willingness to continue participation at all visits. Participants should be aware from the beginning that they can freely withdraw (cease to participate) from the trial at any time. A participant may wish to cease to participate in a *particular* aspect of the trial.

Participants found to be ineligible post randomisation should be followed up according to all trial processes and will still have their data analysed unless they explicitly withdraw their participation.

The changes in levels of participation within the trial are categorised in the following ways:

- **No trial intervention:** the participant would no longer like to receive the trial intervention, but is willing to be followed up in accordance with the schedule of assessments and if applicable using any central UK NHS bodies for long-term outcomes (i.e. the participant has agreed that data can be collected and used in the trial analysis)
- **No trial related follow-up:** the participants no longer wish to attend trial visits in accordance with the schedule of assessments but is willing to be followed up at standard clinic visits and if applicable using any central UK NHS bodies for long-term outcomes (i.e. the participant has agreed that data can be collected at standard clinic visits and used in the trial analysis, including data collected as part of long-term outcomes)
- **No further data collection:** the participant is not willing to be followed up in any way for the purposes of the trial and does not wish for further data to be collected (i.e. only data collected prior to the withdrawal can be used in the trial analysis)

The details of changes of levels in participation within trial (date, reason and category of status change) should be clearly documented in the source documents.

Participants can change their level of participation without giving a reason, although a reason would be very useful in the pilot to help assess whether it is related to the design of the trial.

BCTU should be informed of withdrawal or change in level of participation via the trial exit/change of status form.

## 10 ADVERSE EVENT REPORTING

### 10.1 Definitions

**Table 4:** Adverse event reporting definitions

|                              |          |                                                                                                                                                                                                                                                                                                                                                                                                                                                                                                       |
|------------------------------|----------|-------------------------------------------------------------------------------------------------------------------------------------------------------------------------------------------------------------------------------------------------------------------------------------------------------------------------------------------------------------------------------------------------------------------------------------------------------------------------------------------------------|
| Severity Definitions  | Mild     | Awareness of signs or symptoms that do not interfere with the participant's usual activity or are transient and resolved without treatment and with no sequelae.                                                                                                                                                                                                                                                                                                                                      |
|                              | Moderate | A sign or symptom, which interferes with the participant's usual activity.                                                                                                                                                                                                                                                                                                                                                                                                                            |
|                              | Severe   | Incapacity with inability to do work or perform usual activities.                                                                                                                                                                                                                                                                                                                                                                                                                                     |
| Adverse Event         | AE       | 
Any untoward medical occurrence in a participant or clinical trial subject administered a medicinal product and which does not necessarily have a causal relationship with this treatment.
 
Comment:
 
An AE can therefore be any unfavourable and unintended sign (including abnormal laboratory findings), symptom or disease temporally associated with the use of an investigational medicinal product, whether or not related to the investigational medicinal product.
 |
| Adverse Reaction      | AR       | 
All untoward and unintended responses to an IMP related to any dose administered.
 
Comment:
 
An AE judged by either the reporting Investigator or Sponsor as having causal relationship to the IMP qualifies as an AR. The expression reasonable causal relationship means to convey in general that there is evidence or argument to suggest a causal relationship.
                                                                                                        |
| Serious Adverse Event | SAE      | 
Any untoward medical occurrence or effect that:
 

● Results in death

● Is life-threatening*

● Requires hospitalisation or prolongation of existing hospitalisation

● Results in persistent or significant disability or incapacity

● Is a congenital anomaly/birth defect

                                                                                                                                        |

|                                                      |       |                                                                                                                                                                                                                                                                                                                                                                                        |
|------------------------------------------------------|-------|----------------------------------------------------------------------------------------------------------------------------------------------------------------------------------------------------------------------------------------------------------------------------------------------------------------------------------------------------------------------------------------|
|                                                      |       | 
 
• Or is otherwise considered medically significant by the Investigator**
 
                                                                                                                                                                                                                                                             |
| Serious Adverse Reaction                      | SAR   | An Adverse Reaction which also meets the definition of an SAE                                                                                                                                                                                                                                                                                                                          |
| Unexpected Adverse Reaction                   | UAR   | 
An AR, the nature or severity of which is not consistent with the applicable product information (e.g. Investigator Brochure (IB) for an unapproved IMP or (compendium of) Summary of Product Characteristics (SPC) for a licensed product).
 
When the outcome of an AR is not consistent with the applicable product information the AR should be considered unexpected.
 |
| Suspected Unexpected Serious Adverse Reaction | SUSAR | 
A SAR that is unexpected i.e. the nature, or severity of the event is not consistent with the applicable product information.
 
A SUSAR should meet the definition of an AR, UAR and SAR.
                                                                                                                                                                                  |

\* The term life-threatening is defined as diseases or conditions where the likelihood of death is high unless the course of the disease is interrupted.

\*\* Medical events that may not be immediately life-threatening or result in death or hospitalisation but may jeopardise the participant or may require intervention to prevent one of the other outcomes listed in the definitions above.

## 10.2 Adverse Event recording – general

The recording and reporting of AEs will be in accordance with the UK Policy Framework for Health and Social Care Research, the Principles of Good Clinical Practice (GCP) as set out in the UK Statutory Instrument (2004/1031; and subsequent amendments), the requirements of the Health Research Authority (HRA) and The Medicines for Human Use (Clinical Trials) Regulations 2004 and amendments thereof. Definitions for adverse event reporting are listed in Table 4 in Section 10.1.

It is routine practice to record AEs in the participant's medical notes and it is also recommended that this includes the documentation of the assessment of severity and seriousness and also of causality (relatedness) in relation to the intervention(s) in accordance with the protocol.

## 10.3 Adverse Event reporting in STARFISH

The safety profile for this trial population and interventions are well characterised so a strategy of targeted reporting of AEs will not affect the safety of participants.

Only the following AEs will be reported on the 6 week follow up CRF:

- 
- Further sudden deterioration of hearing after intervention
  - Affective disorders
  - Psychotic reactions
  - Stomach ulcer
  - Acute ear infection (otitis externa or media)
  - New dizziness onset or worsening after intervention
  - New tinnitus onset or worsening after intervention
  - Persistent ear drum perforation at 6 week review
  - Allergic reaction to steroid preparation
  - Allergic reaction to local anaesthetic

Only the following AEs will be reported on the 12 week follow up CRF:

- Persistent perforation of the tympanic membrane

The reporting period for AEs will be from commencement of trial treatment until the 12 week follow up visit (see above for further details of timeline requirements of AE reporting).

The reporting period for Serious Adverse Events (SAEs) will be from commencement of trial treatment until 6 weeks post treatment commencement. All AEs which meet the SAE definition should be reported as per section 10.4.

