### 7.3 Technique for intratympanic injection

**Pre-injection testing:** Immediately prior to the second and third intratympanic injections, a pure tone audiogram will be performed and analysed by the treating clinician.

---

**Stopping the intervention early:** If full recovery has been achieved, based on the pre-injection pure tone audiogram (return to within 10 dBHL of the unaffected ear at 0.5, 1.0, 2.0, 4.0kHz (if contralateral ear has no participant reported pre-existing loss)), the participant and clinician may jointly decide to omit further intratympanic injections. This will be recorded in the intervention Case Report Form (CRF) and the participant will continue within the trial.

**Preparing the medication:** Dexamethasone 3.3mg/ml or 3.8mg/ml should be administered depending on local availability and stored according to local policy. It is recommended that 1ml is drawn up in a 1ml syringe using a wide bore needle. A spinal needle (22-25 gauge) should then be attached to the syringe having removed the needle's central trochar. A slight bend at the hilt of the needle facilitates visualisation along the ear canal under a microscope.

**Positioning the participant for injection:** The procedure should be performed using a microscope or endoscope to visualise the tympanic membrane. The participant should lie recumbent on an examination table at an angle of <20 degrees, with the head turned slightly away from the side to be treated.

**Topical anaesthesia of the eardrum:** Any locally adopted method of local anaesthesia can be used, either in cream (most commonly EMLA (lidocaine 2.5% and prilocaine 2.5%)) or liquid form (most commonly co-phenylcaine spray (5% lidocaine + 0.5% phenylephrine) or xylocaine spray (10% lidocaine)). Local anaesthesia is not needed where there is a perforation of the eardrum.

- EMLA cream - The plunger is removed from a 2ml syringe to allow it to be filled with EMLA cream. The plunger is replaced and a blunt needle bent part way down the shaft to allow better visualisation during the application of EMLA cream to the eardrum under an outpatient microscope. It is important that the cream is in contact with the eardrum avoiding air gaps or bubbles. The anaesthetic can take 30 minutes to be effective.

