## **7.7 Intervention modification or cessation**

As specified in section 7.3, complete resolution of hearing may allow intratympanic steroid treatment to be terminated after only one or two treatments. A rare complication of intratympanic injection is further hearing loss. Where this is observed on pure tone audiometry, no further treatments will be given. In the rare event that a study participant chooses to change treatment type or has a significant side effect from oral steroids and is advised to modify or stop the treatment by their treating clinician this will be recorded. On rare occasions, changes to the intervention schedule may be required based on participant request or adverse events. The allocated interventions may be discontinued if a participant requests to cease treatment or cross over to another arm. Adverse events such as allergic reaction, or a change in patient status, such as development of poor blood glucose control may alter the risk-benefit profile for that individual and the treating clinician should discuss this with the patient and alter the provided intervention, if required. Details of treatment

---

adherence, treatment modifications or treatment discontinuation at the Investigator's discretion should be documented in the source data.

Any modification of the interventions, or cross over to another trial arm will also be recorded on the CRFs.

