#### **Week 1 $\pm 2$ days after first injection**

The following should be performed in the intratympanic injection arm and combination treatment arm:

- Pure tone audiogram (0.5-8.0kHz range)
- 2nd intratympanic injection

NOTE: complete resolution of hearing may allow intratympanic steroid treatment to be terminated after only one treatment

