## 14.2 Analysis of outcomes

A separate Statistical Analysis Plan (SAP) will be produced and will provide a more comprehensive description of the planned statistical analyses. The reporting of the outcomes will be based on the guidelines as published in the Reporting of multi-arm parallel-group randomised trials (22). A brief outline of these analyses is given below.

The objective of the trial is to test the superiority of three interventions:

- Oral steroid
- Intratympanic steroid
- Combination oral and intratympanic steroid

All analysis will have the following two key group comparisons:

- Intratympanic steroid versus oral steroid
- Combination oral and intratympanic steroid versus oral steroid

Oral steroid group will be considered as the control group, i.e. reference category for all analyses. A comparison of intratympanic steroid versus combination oral and intratympanic steroid will also be performed as part of an exploratory analysis for all outcomes.

All primary analyses (primary and secondary outcomes including safety outcomes) will be by intention-to-treat (ITT), i.e. all participants will be analysed in the intervention group to which they were randomised irrespective of adherence to randomised intervention or other protocol deviation. As a secondary (or sensitivity) analysis, a per-protocol analysis will also be carried out for the primary outcome.

To maintain an overall 5% type I error rate, each comparison will be tested at a significance level of 2.5% to account for the increase in the risk of type I error associated with making two key comparisons. Therefore, for the primary outcome and all other secondary outcomes measures, a Bonferroni correction (23) will be applied to account for the increase in the risk of type I error associated with making two key comparisons (i.e. “intratympanic steroid versus oral steroid” and “combination oral and intratympanic steroid versus oral steroid”).

For all outcome measures, appropriate summary statistics and differences between groups, e.g. mean differences, relative risks, absolute differences will be presented, with two-sided 97.5% confidence intervals. Outcomes will be adjusted for the minimisation variables listed in section 6.4.3 and any baseline values (where applicable).

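### Two of the 6-week adverse event items, hearing deterioration and ear infection, are searched for more often in the injection arms, which risks detection bias against injection in the comparison with oral steroid

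*Protocol*

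**What the plan says.** Protocol section 10.3 limits adverse event reporting to a fixed list: "Only the following AEs will be reported on the 6 week follow up CRF". Two of the ten items are "Further sudden deterioration of hearing after intervention" and "Acute ear infection (otitis externa or media". Neither is tied to the week-6 examination, whereas the perforation item in the same list is. The window is wide: "The reporting period for AEs will be from commencement of trial treatment until the 12 week follow up visit".

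The examinations differ by arm. Section 7.3 states: "Immediately prior to the second and third intratympanic injections, a pure tone audiogram will be performed and analysed by the treating clinician". The week 1 and week 2 visits in section 9 open with "The following should be performed in the intratympanic injection arm and combination treatment arm", and Table 3 adds otoscopy at both visits for the same two arms. All arms have an audiogram and otoscopy at weeks 6 and 12. Adverse event monitoring is scheduled at week 6 for everyone and is blank at the injection visits.

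Further hearing loss found at an injection visit has consequences under section 7.7: "Where this is observed on pure tone audiometry, no further treatments will be given". It also bears on per-protocol status (section 7.11.1), and a clinic visit form is completed at each injection visit (section 11.2, Table 9).

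Adverse events are a secondary outcome (section 8.2.2). Section 14.2 states: "All primary analyses (primary and secondary outcomes including safety outcomes) will be by intention-to-treat (ITT"). Oral steroid is the reference group, and section 14.2.2 gives binary outcomes relative risks, 97.5% confidence intervals and p-values.

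**The concern.** An event can be counted only if someone sees it or the participant reports it. A hearing drop or mild ear infection at week 1 or 2 that has gone by week 6 is likely to be seen in an injected participant, who is in clinic with an audiogram and otoscopy. The result is read by the treating clinician, who knows the allocation, and a form is completed. The same event in an oral-arm participant has no scheduled clinic examination to reveal it. It reaches the 6-week form only if it was noticed and is recalled, or was noted elsewhere.

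Further hearing loss is a harm that the protocol itself attaches to injection (section 7.7; Table 5). An excess in the injection arms would look like confirmation, although part of it could come from the extra examinations. Both key comparisons have oral steroid as reference, so both are exposed. The exploratory intratympanic versus combined comparison is not, because those two arms share the schedule.

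**Working it through.** **1. Scheduled clinic examinations from treatment start to week 6** (Table 3; sections 7.3 and 9)

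| Arm | 2nd injection visit | 3rd injection visit | Week 6 | Total |
|---|---|---|---|---|
| Oral | 0 | 0 | 1 | 1 |
| Intratympanic | 1 | 1 | 1 | 3 |
| Combined | 1 | 1 | 1 | 3 |

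The counts hold for audiograms and for otoscopies. Three is the full-course figure; participants who stop injections early may have fewer.

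**2. The plan's own figures.** The protocol states no adverse event rate, so there is none to reproduce. The number analysed per arm is taken from section 14.1 and does reproduce. With a difference of 10, SD 25, two-sided alpha 0.025 and 90% power, the normal approximation gives 156 per arm. With the t distribution, 157 is the first size to reach 90% (90.1%; 156 gives 89.9%). Then 157/0.9 = 174.4, rounded up to 175, and 3 × 175 = 525.

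**3. Size with partial capture in every arm (assumed inputs).** Suppose the true event rate p is the same in all arms. Let s be the share of events captured in every arm by week 6, through examination, recall or notes. Let e be the chance that each extra visit finds an event otherwise missed. Then

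- oral arm: p·s
- injection arm: p·[s + (1 − s)(1 − (1 − e)²)]
- apparent relative risk: 1 + [(1 − s)/s]·[1 − (1 − e)²], which does not depend on p.

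Low end, s = 0.9 and e = 0.1: 1 + (0.1/0.9)(0.19) = 1.02. High end, s = 0.5 and e = 0.5: 1 + (0.5/0.5)(0.75) = 1.75.

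| s | e = 0.1 | e = 0.3 | e = 0.5 |
|---|---|---|---|
| 0.9 | 1.02 | 1.06 | 1.08 |
| 0.7 | 1.08 | 1.22 | 1.32 |
| 0.5 | 1.19 | 1.51 | 1.75 |

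At p = 10% the spurious risk difference runs from 9.19% − 9.00% = 0.19 points to 8.75% − 5.00% = 3.75 points. With 157 per arm the high end is 157 × 0.0875 = 13.7 events against 157 × 0.05 = 7.9.

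**4. Chance of a false signal against injection.** This is Φ[(RD − 2.24·SE₀)/SE₁], where RD is the spurious risk difference, SE₀ the pooled and SE₁ the unpooled standard error at 157 per arm, and 2.24 the two-sided 2.5% critical value. With no bias it is 0.025/2 = 1.25%.

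| True rate | s = 0.9, e = 0.1 | s = 0.5, e = 0.5 |
|---|---|---|
| 5% | 1.4% | 9.2% |
| 10% | 1.5% | 17.6% |
| 20% | 1.6% | 37.7% |

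**5. A ceiling.** If each audiogram independently flags a transient drop with probability f, every flag counts as an event, everyone has three tests and the oral arm adds nothing by self-report, the injection arms show 1 − (1 − f)³ against f. At f = 2% this is 5.9% v 2.0% (ratio 2.9); at 5%, 14.3% v 5.0% (2.85); at 10%, 27.1% v 10% (2.7).

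**The case against.** The strongest reply is that ascertainment is common. Both items are reported once, on the same form, at a visit where every arm has otoscopy and an audiogram, and no adverse event monitoring is scheduled at the injection visits. This largely stands for lasting events. It does not cover events that resolve earlier, because neither item is restricted to findings at week 6 and the reporting window opens at treatment start.

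Second, the hearing item says sudden deterioration, and the protocol's Definitions table gives sudden loss a demanding meaning. A real sudden drop is likely to be noticed and reported in any arm. This also has force: ordinary test-retest variation should not count. But section 10.3 neither refers to that definition nor sets an audiometric threshold, so what counts is left to judgement.

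Third, hearing harm is measured without this asymmetry elsewhere. The change in pure tone average at weeks 6 and 12 is obtained in all arms by blinded audiologists, and would be read beside any excess of events. That limits the damage but does not correct the adverse event comparison. The weekly home tests help little, since they are optional and not named as a source of adverse events.

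Fourth, counting rules are often left to the statistical analysis plan, which is not available here. But the visit schedule, the event items and the comparison with oral steroid are set in the protocol. Nothing in it shows that the source of detection is recorded, and a later analysis cannot separate sources that were not collected.

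A reader might infer that the whole safety comparison is biased against injection, or that events would appear nearly three times as often. The documents support neither. The concern is established for two of ten items; affective disorder, psychotic reaction and stomach ulcer, for example, are not found by audiogram or otoscopy. The threefold figure needs the ceiling assumptions in step 5. A reader might also take the absence of a hearing-deterioration item at week 12 as part of this bias. That omission is the same in every arm, and the week-12 audiogram feeds the primary outcome.

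**Conclusion.** The point holds as a risk of detection bias in two items: hearing deterioration and acute ear infection. The unequal schedule, three examinations against one, is a matter of record. For a given true rate, its effect on these items runs against injection. It concerns transient or symptom-free events at weeks 1 to 2 that are gone by week 6; persisting events can be found equally.

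The size cannot be settled from the protocol. With 50% to 90% of events captured in every arm and each extra visit finding 10% to 50% of the rest, the spurious relative risk is 1.02 to 1.75. Larger values need more extreme assumptions, with the oral arm's events largely going unreported. At a true rate of 10%, the chance of a false signal against injection is about 1.5% to 18%, against 1.25% without bias. These capture rates and event rates are assumptions. The primary outcome and the sample size are not affected.

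**What to change.** 1. **Record how each event was found.** Keep reporting all events. Add one field to the 6-week form for these two items: injection visit, week-6 examination, or participant report.
2. **Hearing deterioration.** Base the between-arm comparison on the audiograms every arm has: the proportion whose four-frequency average is worse than baseline by a pre-stated amount, at week 6 and at week 12. For example, 10 dB is the change threshold already used in Table 2.
3. **Ear infection.** Compare findings at the common week-6 otoscopy. Whether an infection was treated should not be the criterion, because infections seen at an injection visit can be treated there and the asymmetry would return.
4. **All events.** Report the all-events comparison beside these, show events found only at injection visits separately, and state that it is subject to unequal ascertainment.

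The cost is one form field, one extra analysis and a few lines of text. No test or visit is added and no treatment rule changes. The limitation is that the common-visit comparison misses early transient events, and misses a drop from an improved level that stays above baseline. Either could be a real harm of injection, so the all-events table must be kept.
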